#### Exclusion criteria

Participants will be excluded if they have other diseases that also cause breathlessness or dyspnea, such as bronchiectasis, cor-pulmonale, pulmonary fibrosis, tuberculosis, pulmonary abscess, chronic obstructive pulmonary disease and so on. Participants will not be eligible if the female are in the duration of pregnancy or lactation. The following conditions are also excluded items: Complicated with serious life-threatening diseases, such as heart and brain blood vessels, liver, kidney and hematopoietic system disease and psychotic patients; Hormone-dependent type patients, or the people who used adrenal cortical hormone (intravenous, intramuscular injection, subcutaneous injection and oral administration) within 4 weeks before recruiting.

### Treatment protocol

#### Heat-sensitive moxibustion

Moxibustion will be performed by certified acupuncture medical doctors at 12 centers. Qualified specialists of acupuncture in traditional Chinese medicine with at least five years of clinical experience will perform the acupuncture in this study. All treatment regimens will be standardized between 12 centers practitioners via video, hands-on training and internet workshops. Participants will be randomly assigned to the heat-sensitive moxibustion group, or the drug group. In the former group, a 22 mm (diameter) × 160 mm (length) moxa-sticks (Jiangxi Hospital of Traditional Chinese Medicine, China) will be used. The patient is usually in the comfortable position for treatment, with 24°C~30°C temperature in the room. He should wear loose clothes.

For the heat-sensitive moxibustion group, the moxa-sticks are lit by the therapist and held over the rectangle area which consist of two outer lateral lines of dorsal Bladder Meridian of Foot-Taiyang, and two horizontal lines of BL13(Fei Shu) and BL17 (Ge Shu);6 inch outer the first and second rib gap of anterior chest. The warming suspended moxibustion about distance of 3 cm above the skin are used to search the acupoint heat-sensitization phenomenon. The following patients sensation will suggest the special heat-sensitization acupoint: diathermanous sensation due to moxa-heat, defining as the heat sensation conducting from the Moxa local skin surface into deep tissue, or even into the thoracic cavity; expand heat sensation due to moxa-heat, defining as the heat sensation spreading the surrounding little by little around the moxa point; transfer heat sensation due to moxa-heat, defining as the heat sensation transferring along some pathway, or even to the arms. The therapists mark the point as heat-sensitive acupoint. We try our best to seek all the special acupoints in each patient by the repeated manipulation.

The therapists begin to treat patients from the most heat-sensitive intensity acupoint. Treatment sessions end when patients are feel the acupoint heat-sensitization phenomenon disappeared. Generally speaking, we find the time range from 30~60 minutes. In 1^st ^month, patients receive the treatment once a day in the first eight days, and 12 times treatment in the next twenty-two days. Treatments will be given 15 times a month for the remaining two months.

#### Drug group

In recent years, considerable insight has been gained in to the optimal management of adult asthma. Those with persistent asthma are usually not well controlled without inhaled corticosteroids (ICS). Adding a long-acting beta-agonist (LABA) to ICS appears to be well controlled [33]. The combination of an ICS and LABA is preferred in these patients, and is better than doubling or even quadrupling the dose of ICS to achieve better asthma control and reduce exacerbation risks [34,35]. Two such combinations, salmeterol xinafoate and fluticasone propionate (SFC, Seretide(tm)) and formoterol and budesonide (FBC, Symbicort(tm)) are widely used and have been shown to be effective in controlling asthma of varying severity in adults and children[36-38].

Therefore, we selected the Seretide Accuhaler, containing two medicines, fluticasone propionate and salmeterol xinafoate, which is the mainstay of current asthma treatment. This drug is recommended by GINA as a regular treatment. Our trial uses salmeterol/ﬂuticasone 50 μg/250 μg twice a day. Patients receive the treatment for a total of 180 sessions over 90 days.

### Statistical methods

#### Statistical analysis plan

We will conduct analysis on an intention-to-treat basis, including all randomized participants with at least one measurable outcome report. Analyses will be conducted using 2-sided significance tests at the 5% significance level. An analysis using the Cochran-Mantel-Haenszel procedure will be done to asses center effect. The statistician conducting the analyses will remain blind to treatment group and data will only be unblinded once all data summaries and analyses are completed. All analyses will be conducted in the SAS statistical package program (ver. 9.1.3).

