##### Dropped or missing data

Reasons for dropped or missing data will be explored by descriptively. Missing data will be replaced according to the principle of the last observation carried forward.

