##### Follow-up data

The primary outcome will be the ACT scores. The primary analysis will compare the two groups in 3 months. A secondary analysis will compare the two groups at 6,9 months to assess if any differences between groups have been maintained over time.

Loss to follow-up is likely to lead to biased estimates of intervention effect. We will try to avoid bias due to attrition by carefully following up the participants in both groups. We will phone participants who fail to complete questionnaires after a second reminder. We anticipate a 20% loss to follow-up in this trial, and will implement procedures to minimize loss to follow-up and patient withdrawal, and where possible, we will collect information on reasons for patient withdrawal.

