#### Sample size

We wished to estimate the sample size according to non-inferiority clinical trial between the heat-sensitive and drug group. Sample size depends on the level of confidence chosen, the risk of type II error (or desired power), and δ. The parameter margin of non-inferiority δ can be specified as a difference in means or proportions. It is often chosen as the smallest value that would be a clinically important effect. To determine δ, we carried out a small sample pilot study previously. The primary endpoint chosen was ACT. The result of outcome showed difference in means between the two groups approximately was 0.45. The choice of δ = 0.15 (30% of Δ) appeared to be reasonable based on clinical relevance and statistical judgment.

If we apply a two-sided 5% significance level(δ = 0.15, α = 0.05, β = 0.2), 95% power the calculated required sample size is approximately 120 participants in each group, according to the following equation. Allowing for a 20% loss to follow up, a total of 144 participants will be required in each group, with 288 participants in total.

$$n=2\times \frac{{\left(U_{\alpha }+U_{\beta }\right)}^{2}}{\gamma^{2}}\times P(1-P)$$

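### The set labelled intention-to-treat rests on an undefined outcome report, so it either selects patients after randomisation or carries an untreated score to the primary comparison

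*Protocol article*

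**What the plan says.** Under Statistical analysis plan the protocol article says: "We will conduct analysis on an intention-to-treat basis, including all randomized participants with at least one measurable outcome report". The label and the restriction stand in one sentence, and the report that qualifies a patient is not defined.

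Under Dropped or missing data it adds: "Missing data will be replaced according to the principle of the last observation carried forward". Under Follow-up data it says: "We anticipate a 20% loss to follow-up in this trial". The 20% is not split by arm or by time. The same section accepts that attrition can bias the estimated effect, and places the primary comparison of ACT at 3 months.

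Under Primary outcome, ACT is scheduled before treatment and at days 15, 30, 60 and 90. Under Sample size the trial is planned as non-inferiority: "We wished to estimate the sample size according to non-inferiority clinical trial between the heat-sensitive and drug group". The margin is given as "The choice of δ = 0.15 (30% of Δ) appeared to be reasonable".

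**The concern.** An intention-to-treat analysis compares everyone randomised, as allocated. A rule that depends on having an outcome record gives something else, and what it gives depends on the reading.

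- **An on-treatment score is required.** The earliest is at day 15, so a patient who leaves before then is removed. LOCF cannot help a patient who is outside the analysis set.
- **The baseline score is enough.** Almost nobody is removed, but a patient who leaves before day 15 enters the 3-month comparison with a score taken before any treatment.

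Early departure could plausibly differ between arms. By day 15 the moxibustion arm is scheduled for eight daily sessions plus, if the next 12 are spread evenly over 22 days, about 7 × 12/22 = 3.8 more, each generally 30 to 60 minutes. The control arm uses an inhaler. The assessor is blinded, but patients can tell moxibustion from an inhaler, and they complete the ACT themselves. What is at stake is whether the primary estimate is the comparison of randomised groups that its label promises.

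**Working it through.** **Inputs from the article.** 144 per arm; 20% anticipated loss; margin 0.15; ACT at baseline and days 15, 30, 60 and 90; primary comparison at 3 months. The planned 144 reproduces as 120 × 1.20. Twenty per cent of 144 is 28.8 patients per arm.

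**Not in the article.** The share of each arm with no on-treatment ACT, and how those patients would have scored. The 20% is total loss. Anyone lost after a day-15 score stays in the set through LOCF, so 20% is only an upper reference. The shares and deficits below are assumptions.

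**Reading 1: an on-treatment score is required.** Let q be the share of an arm excluded, and D the mean ACT of its retained patients minus that of its excluded patients. The full-arm mean is the retained mean minus q × D, so exclusion raises the arm mean by q × D. For moxibustion (A) minus drug (B):

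bias = qA × DA − qB × DB

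If exclusion acts in one arm only, the deficit that gives a shift of 0.15 is D = 0.15 / q:

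| Share excluded | Patients of 144 | D giving 0.15 |
|---|---|---|
| 2% | 2.9 | 7.5 |
| 5% | 7.2 | 3.0 |
| 10% | 14.4 | 1.5 |
| 20% | 28.8 | 0.75 |

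Across 3% to 7% excluded and deficits of 2 to 4 points, the one-arm shift runs from 0.03 × 2 = 0.06 to 0.07 × 4 = 0.28.

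If exclusion acts in both arms with D = 3:

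- 5% in each: 0.05 × 3 − 0.05 × 3 = 0
- 10% in A, 5% in B: 0.30 − 0.15 = 0.15
- 10% in A, 2% in B: 0.30 − 0.06 = 0.24

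Swapping the arms reverses the sign.

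**Reading 2: the baseline score counts.** Let q now be the share whose baseline is carried forward, and G the day-90 score they would have had minus their baseline. The arm mean moves by −q × G. With q = 5% and G = 3 in arm A only, that is −0.15, against moxibustion. If G is negative the sign turns; if q × G is equal in both arms the bias is 0.

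**Scale of the yardstick.** The Sample size section takes the margin from ACT means: "The result of outcome showed difference in means between the two groups approximately was 0.45". Its printed formula, however, contains P(1−P), which belongs to a proportion. On a proportion scale, excluding a share q of one arm can shift its proportion by at most q, so a one-arm shift above 0.15 needs more than 15% excluded with an extreme contrast in outcome. The comparison with 0.15 is therefore strong only if the margin is in ACT points.

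**The case against.** The restriction is disclosed in the same sentence as the label, so part of this is about naming. ACT is taken before treatment, so the reading in which nearly everyone is included is open, and what remains there is an objection to LOCF. The article also plans reminders, telephone contact, and collection of reasons for withdrawal. The sizes rest on assumed shares and deficits. With 120 per arm and an assumed SD of 3 to 4, the standard error of the difference is 3 × √(2/120) = 0.39 to 4 × √(2/120) = 0.52, so 0.15 is under half a standard error. It looks large because the margin is small, which is a separate matter.

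Most of this stands, and it limits the point to an ambiguous, mislabelled rule with a weak missing-data method. It does not remove the point. The article itself states the rule and the LOCF method, so this is not detail left to a fuller plan, and both readings fall short of the label. Follow-up effort reduces missing data but does not decide how the remainder is analysed.

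A further objection concerns the remedy. A mixed model or standard multiple imputation assumes missing at random. It predicts patients with only a baseline score from retained patients with similar baselines, so it does not by itself correct for leavers who would have done worse. That is right, and it is why the fix includes a sensitivity analysis for departures from that assumption.

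**Conclusion.** The point holds as a fault of definition and method that should be corrected before the data are seen. Followed as written, the rule either selects on events after randomisation or carries an untreated score into the primary comparison. Neither is a sound version of the intention-to-treat comparison claimed.

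The size is not determined by the article. A shift of 0.15 ACT points needs, for example, 5% excluded in one arm with a 3-point deficit, both assumed; with equal shares and deficits it is zero.

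A reader might infer that the plan certainly discards randomised patients, that this favours moxibustion, and that it uses up the whole margin. The article does not support that. The baseline reading is open, and under it the sign can be the opposite. Patients allocated to the drug may also leave early. The 20% is not the share without a report, and the scale of the 0.15 margin is unclear.

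**What to change.** 1. Define the primary set as all randomised participants, analysed as allocated.
2. Replace exclusion plus LOCF with a mixed model for repeated measures that has baseline ACT in the response vector, or with multiple imputation, so that patients without later scores remain in the analysis.
3. Report, by arm, the number without any post-baseline ACT.
4. Add a sensitivity analysis for departures from missing at random, for example delta-adjusted imputation that penalises the moxibustion arm, which suits a non-inferiority question.
5. Keep the present set as a sensitivity analysis, labelled modified intention-to-treat, and state whether its qualifying report must be post-baseline.

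The cost is revised wording, a little more analysis work and possibly slightly wider intervals. Recruitment, visits and treatment do not change.

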#### Secondary outcomes

Measurement of lung function provides an assessment of the severity, reversibility, and variability of airflow limitation. Forced expiratory volume in 1 s (FEV1) and peak expiratory flow (PEV) will be used in this trial. Attack frequency also will be assessed. These outcomes also will be assessed before treatment and at days 90 in the treatment period. Follow-up visit will be at 3, 6 months after the last treatment session. Adverse event information will be collected at each clinic visit.

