## Discussion

To our knowledge, the goal of asthma care is to achieve and maintain control of clinical manifestations of the disease for prolong periods. When asthma is controlled, patients can prevent most attacks, avoid troublesome symptoms day and night, and keep physically active [1]. Acupuncture therapy was often perceived as an effective option to control asthma successfully by patients with chronic asthma. The use of acupuncture in asthma patients is increasing as an adjunct and also as a substitute for effective and proven therapies [39]. In China, moxibustion are considered as an ancient treatment to prevent and control asthma, and still widely used today. A number of clinical trial suggested moxibustion as one of traditional acupuncture therapy, should effective in the treatment of asthma. But the methodological problems of published trials haunt us the trust of moxibustion. Therefore, we design this rigorous clinical trials meeting the CONSORT statement and guidelines to guarantee a high internal validity for the results.

At present, various conventional medications are used to slow down and control with the disease. An ICS/LABA combination in a single inhaler represents a safe, effective and convenient treatment option, and recommended by GINA. So, we selected the fluticasone/salmeterol (seretide) as the control treatment in the protocol. Actually, the aim of this trial is to search an effective CAM treatment to control asthma, as good as conventional drug. The focused features of moxibustion are low cost, less adverse event and low risk.

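### Intention-to-treat is the only analysis basis in a non-inferiority trial, and nothing says how day-90 ACT is handled after a patient starts a non-assigned steroid or controller

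*Protocol article*

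**What the plan says.** All references are to the protocol article.

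- **Analysis basis** (Statistical analysis plan): "We will conduct analysis on an intention-to-treat basis, including all randomized participants with at least one measurable outcome report". No other analysis set is named. The same section adds: "Analyses will be conducted using 2-sided significance tests at the 5% significance level".
- **Primary comparison** (Follow-up data): ACT in the two groups at 3 months.
- **Missing scores** (Dropped or missing data): LOCF.
- **Purpose** (Sample size): "We wished to estimate the sample size according to non-inferiority clinical trial between the heat-sensitive and drug group". The margin is set there: "The choice of δ = 0.15 (30% of Δ) appeared to be reasonable". The Discussion gives the aim: "Actually, the aim of this trial is to search an effective CAM treatment to control asthma, as good as conventional drug".
- **Expected control without inhaled steroid** (Drug group): "Those with persistent asthma are usually not well controlled without inhaled corticosteroids (ICS". The moxibustion regimen described under Heat-sensitive moxibustion contains no drug.
- **Attacks** (Secondary outcomes): "Attack frequency also will be assessed".
- **Other asthma treatment:** the Inclusion criteria have relief medication stopped during run-in and treatment. The Exclusion criteria restrict systemic corticosteroid only in the four weeks before entry. No section says what happens to a patient's scores if a steroid or controller is started after randomisation.

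**The concern.** Keeping every randomised patient in the allocated arm is sound in itself. The difficulty lies in what it does to a non-inferiority comparison when patients who fail on the test treatment receive drugs of the comparator's class. In a superiority trial, such added treatment shrinks the observed difference and makes the test conservative. In a non-inferiority trial, the same shrinkage works in favour of the claim.

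The plan's own account of persistent asthma makes added treatment foreseeable in an arm assigned no inhaled steroid for 90 days. A patient who starts a controller on day 40, say, and attends on day 90 has a complete ACT score. Intention-to-treat with no further rule enters that score as a moxibustion result. At stake is whether a finding that moxibustion matches the drug would reflect moxibustion alone, or partly drug treatment given because moxibustion had failed.

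**Working it through.** **1. The plan's own figure.** The Sample size section uses n = 2(Uα + Uβ)² / γ² × P(1 − P). With γ = δ = 0.15, two-sided α = 0.05 and β = 0.2:

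2 × (1.960 + 0.842)² / 0.15² = 2 × 7.849 / 0.0225 = 697.7, so n = 697.7 × P(1 − P).

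P is not given, so the stated 120 per group cannot be reproduced. It requires P(1 − P) = 120 / 697.7 = 0.172, that is P of about 0.22 or 0.78. The section also states 95% power; on that reading the multiplier is 1155.1 and P would be about 0.12 or 0.88.

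The illustration below therefore takes the design at its word: 120 analysable patients per arm and 80% power. That fixes the ratio of margin to standard error at δ/SE = 1.960 + 0.842 = 2.80, so no ACT standard deviation is needed.

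**2. Which rule catches a patient who switches.**

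| Situation at day 90 | Rule that applies | Score used |
|---|---|---|
| Added drug, attends | Intention-to-treat | Observed ACT, after the added drug |
| Added drug, withdrawn, no later score | LOCF | Last earlier ACT |

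The documents do not say which situation such a patient falls into. Only the first produces the bias described.

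**3. Size of the effect, as an illustration.** Suppose that without added drug moxibustion is truly worse by exactly the margin, so a correct procedure declares non-inferiority 2.5% of the time. This assumes that non-inferiority is judged by the limit of a two-sided 95% confidence interval, which the article does not spell out. Let a share r of moxibustion patients switch and regain a fraction e of the deficit. The expected deficit becomes (1 − r·e)δ, and

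false non-inferiority rate = Φ(−1.96 + r·e·2.80).

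For r = 10% and e = 1: Φ(−1.96 + 0.28) = Φ(−1.68) = 4.7%. For r = 20% and e = 1: Φ(−1.96 + 0.56) = Φ(−1.40) = 8.1%.

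| Recovery e (assumed) | r = 10% | r = 20% | r = 30% |
|---|---|---|---|
| Full (1) | 4.7% | 8.1% | 13.1% |
| Half (0.5) | 3.4% | 4.7% | 6.2% |
| None (0) | 2.5% | 2.5% | 2.5% |
| Worse (−0.5) | 1.8% | 1.3% | 0.9% |

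With all 144 per arm analysed at the same standard deviation, the full-recovery figures at 10% and 20% are 4.9% and 8.9%. If 120 per arm is instead taken to give the stated 95% power, they are 5.5% and 10.8%. Both r and e are assumptions; the documents supply neither.

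**The case against.** Several points on the other side have force.

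- **A reader might infer that the plan states ACT is scored whatever drug the patient is taking.** It does not. That follows from the ordinary meaning of intention-to-treat, not from the wording.
- **LOCF may already do part of the work.** If patients who start another controller are withdrawn and not scored again, the score before the switch is carried forward, close to what the companion analysis would do. This stands as a possibility. Nothing says these patients are withdrawn, though, and if centres differ, the same failure would be scored in two ways.
- **A reader might infer that moxibustion patients will be switched, or how often.** No section provides for it or gives a frequency. The remark about control without inhaled steroid is background for choosing the comparator. It makes switching foreseeable and no more.
- **The direction is not certain.** ACT item 4 lowers the score for rescue inhaler or nebulizer use. Every item looks back four weeks, so a late attack still depresses day 90. Drug-arm patients may also receive added treatment. Against this, item 4 is one of five items and does not ask about a controller or oral steroid. The drug arm already receives an inhaled steroid with a long-acting beta-agonist, so it probably has less to gain.
- **A much larger bias is tempting to claim** by adding an assumed gain in ACT points to the standard deviation of about 0.41 that the sample size equation implies (√0.172). That is unsound. The equation is for a proportion, while the ACT total runs from 5 to 25 (five items scored 1 to 5). Nor should a shift larger than the deficit be called dilution, since it would put moxibustion ahead of the drug.
- **A fuller plan may cover this.** If so, the article's wording need only be aligned with it.

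**Conclusion.** The point holds in a limited form. Intention-to-treat is a legitimate choice, and the article's figures contain no error on this matter. The weakness is that intention-to-treat stands alone in a trial sized for non-inferiority, and no rule separates ACT under the assigned treatment from ACT after a non-assigned systemic corticosteroid or controller. The likely effect is a bias towards declaring moxibustion non-inferior.

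Its size cannot be derived from the documents. The illustrative rise from 2.5% to about 5–8% rests on 10–20% switching in the moxibustion arm only, full recovery to the drug-arm mean, a true deficit equal to the margin, 120 per arm and 80% power. With no recovery there is no inflation, and if switchers score worse the bias reverses.

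**What to change.** 1. Keep the intention-to-treat comparison of all randomised patients at 3 months.
2. Record on the case report form, in both arms, the start date of any asthma drug outside the assigned treatment.
3. Prespecify a companion analysis, applied identically to both arms, in which ACT after a non-assigned systemic corticosteroid or controller is not used as observed. One option is to carry forward the last ACT before the added drug, with a more pessimistic failure score as a sensitivity analysis. A per-protocol set would not serve this purpose, because it removes these patients instead of counting them.
4. Claim non-inferiority only if both analyses meet the margin.
5. Reconcile the Inclusion criteria, Statistical analysis plan, and Dropped or missing data sections on patients who receive other asthma treatment, including whether they stay in follow-up and which score is used. This concerns the handling of scores; no rule on who should receive such drugs is proposed.

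The cost is some analysis wording, one added date field, a small loss of power from requiring two analyses to agree, and a somewhat less favourable estimate for moxibustion. No extra visits are needed.
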